### Patient selection and enrollment criteria

#### Target disease

Liver tumors (primary or metastatic liver cancer)

#### Inclusion criteria

Primary registrationScheduled for hepatic resection for liver tumors (primary or metastatic liver cancer);Aged ≥20 years at the time of consent;Performance status score of 0 or 1;White blood cells ≥2000/mm^3^, hemoglobin ≥7.0 g/dl, platelets ≥30 000/mm^3^, total bilirubin ≤5.0 mg/dl, and creatinine ≤2.0 mg/l;Written informed consent.Secondary registrationDrainage volume of ≥5 ml/BW 1 kg/day on postoperative day 1.

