Based on the clinical practice guidelines for liver cirrhosis published by the Japanese Society of Gastroenterology, spironolactone is the first choice for patients with frequent drainage after hepatic resection, and furosemide is used when the effect of spironolactone is unsatisfactory^12^. However, spironolactone is refractory in ~15–20% of patients with ascites and does not respond to diuretic therapies^13^. Additionally, the use of high doses of spironolactone causes renal function deterioration and mineral abnormalities^14^. Patients with refractory ascites can be treated with various therapies, including concentrated ascites reinfusion therapy, peritoneovenous shunting, and transjugular intrahepatic portosystemic shunting; however, their efficacy is limited^15–17^.

Recently, the efficacy of the additional use of tolvaptan in patients with cirrhosis has been demonstrated. In patients who do not respond to existing diuretic therapy, tolvaptan results in weight loss, ascites reduction, increased urine output, and improved symptoms related to edema in ~60% of patients^18–21^. Several studies have reported that tolvaptan use in patients with refractory ascites improves their long-term prognosis^22,23^. Furthermore, tolvaptan results in significantly lower renal dysfunction in patients with ascites effusions due to cirrhosis treated with tolvaptan compared with those not treated with tolvaptan^24,25^.

Tolvaptan is an orally selective vasopressin type 2 receptor antagonist that inhibits water reabsorption by decreasing aquaporin 2 expression in the collecting duct, thereby promoting free water excretion without increasing sodium excretion^26,27^. It has also been reported to maintain renal blood flow during diuresis without activating the renin-angiotensin-aldosterone system^28,29^. As tolvaptan can improve congestive symptoms without impairing renal function, its efficacy in patients with acute heart failure and complications after cardiac surgery is also attracting attention^30,31^.

For these reasons, we hypothesized that the prophylactic use of tolvaptan in patients with refractory ascites after hepatic resection would be effective in controlling ascites and protecting renal function. However, there are no reports regarding the efficacy of tolvaptan in patients with refractory postoperative ascites.

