### Study objectives and endpoints

The primary endpoint of this study will be the maximum change in body weight (BW) after hepatic resection relative to the preoperative baseline. We consider using drainage volume as the primary endpoint; however, drainage volume is highly variable and inaccurate. Weight change correlates well with drainage volume and has less variability; hence, we use weight change as the primary endpoint. The secondary endpoints will be the following: (1) drainage volume, (2) abdominal circumference, (3) urine output, (4) postoperative complication rate (heart failure and respiratory failure), (5) number of days required for postoperative weight gain because of ascites to decrease to preoperative weight, (6) change in improvement of postoperative pleural effusion, (7) total amount of albumin or fresh frozen plasm (FFP) transfusion, (8) type and amount of diuretics used, and (9) postoperative hospitalization days.

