#### Exclusion criteria

Primary registrationPreoperatively taking tolvaptan;History of serious drug hypersensitivity or hypersensitivity to any component of tolvaptan or similar compounds;Difficulty with fluid intake or adequate hydration;Pregnant or may become pregnant;Severe ischemic heart disease or severe valvular heart disease (New York Heart Association classification ≥III);Severe hepatic cirrhosis (liver damage C);Renal dysfunction (creatinine ≥2.0) and hyperkalemia (potassium > 5.5 mEq/l);Dyspnea requiring oxygen administration due to severe respiratory impairment (Hugh–Jones classification ≥IV), interstitial pneumonia, or pulmonary fibrosis;Serious preoperative complications, such as infection or gastrointestinal bleeding;Requiring gastrointestinal anastomosis, biliary reconstruction, lymph node dissection, revascularization, or complicated resection of other organs other than the gallbladder;Psychosis or psychiatric symptoms that make study participation difficult.Secondary registrationDifficulty with fluid intake or adequate hydration;Serious postoperative complications, such as infection or gastrointestinal bleeding;Performed gastrointestinal anastomosis, biliary reconstruction, lymph node dissection, revascularization, or complicated resection of other organs other than the gallbladder.

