### Interventions

#### Tolvaptan oral administration

For patients with ascites drainage ≥5 ml/BW 1 kg on postoperative day 1, tolvaptan 7.5 mg will be added to potassium canrenoate 200 mg (or spironolactone 50 mg) starting on postoperative day 2. Tolvaptan will be administered once daily in a glass of water. When a patient forgets to take a dose of tolvaptan, the patient will take tolvaptan immediately if it is within 4 h of the scheduled dose; if ≥4 h has passed, the patient will resume taking the drug as usual the next time. The dose may be reduced or discontinued if possible as the disease improves.

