#### Concomitant diuretics

Potassium canrenoate 200 mg intravenously once daily or spironolactone 50 mg orally once daily will be the basic treatment on postoperative day 1. Similar to tolvaptan, potassium canrenoate can be reduced or discontinued as required as symptoms improve. If the ascites is difficult to control, potassium canrenolate or hurosemide may be added. Other concomitant therapies commonly used in daily practice are not restricted. The treatment duration for refractory ascites, including oral tolvaptan, should range from 2 weeks to 1 month.

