### Follow-up and assessment of efficacy

#### Assessment tools

The maximum perioperative weight change will be the primary endpoint of this study. The secondary endpoints will include drainage volume, abdominal circumference, and urine output. Blood tests, chest radiography, and computed tomography (CT) will be used to evaluate the incidence of postoperative complications and changes in the improvement of postoperative pleural effusion. To assess patient safety, blood sodium and potassium levels and liver and renal functions will be evaluated.

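### The creatinine limit has the wrong unit at inclusion and none at exclusion, both lists contain 2.0, and the link to potassium is ambiguous

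*Protocol article*

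**What the plan says.** Both limits are in the primary (preoperative) registration lists of the protocol article.

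- **Inclusion criteria:** "total bilirubin ≤5.0 mg/dl, and creatinine ≤2.0 mg/l". In the same line hemoglobin is in g/dl and bilirubin in mg/dl.
- **Exclusion criteria:** "Renal dysfunction (creatinine ≥2.0) and hyperkalemia (potassium > 5.5 mEq/l"), printed as one item. Potassium has a unit and creatinine has none.

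The secondary registration criteria, applied after surgery, repeat neither limit. No other section gives a creatinine or potassium threshold.

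The background treatment is as follows.

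- **Concomitant diuretics:** "Potassium canrenoate 200 mg intravenously once daily or spironolactone 50 mg orally once daily will be the basic treatment" on postoperative day 1. The section also states: "If the ascites is difficult to control, potassium canrenolate or hurosemide may be added".
- **Tolvaptan oral administration:** "tolvaptan 7.5 mg will be added to potassium canrenoate 200 mg (or spironolactone 50 mg) starting on postoperative day 2".
- **Introduction:** "the use of high doses of spironolactone causes renal function deterioration and mineral abnormalities". It does not say whether the planned doses count as high.

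**The concern.** There are three defects in two lines of operative eligibility text.

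1. **Unit.** Creatinine is in mg/l where the neighbouring limits are per decilitre, and the exclusion gives no unit that would correct it.
2. **Boundary.** Once both limits share a unit, the value 2.0 lies in both lists. If the exclusion means two separate grounds, this is a contradiction at that one value.
3. **Connector.** The exclusion joins renal dysfunction and hyperkalemia with *and*. Read literally, a patient must have both to be excluded, so high potassium alone excludes nobody.

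Points 2 and 3 do not both apply in full. With two grounds the potassium gap disappears. With a literal *and* the conflict at 2.0 remains only when potassium is also above 5.5.

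What is at stake is mainly safety at entry. This line holds the only potassium entry limit in the article, and every treated patient is to receive potassium canrenoate or spironolactone. Preoperative blood tests may be up to 90 days old (Observation and examination schedule), and the limits are not applied again at secondary registration. This one line is therefore the whole stated renal and potassium screen.

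**Working it through.** No sample size, power or significance figure enters this point, so there is no planned figure of that kind to reproduce. The check is a unit conversion, a boundary comparison and a truth table.

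**Inputs**

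| Item | Value | Source |
|---|---|---|
| Creatinine, inclusion | ≤2.0 mg/l | Inclusion criteria |
| Creatinine, exclusion | ≥2.0, no unit | Exclusion criteria |
| Potassium, exclusion | >5.5 mEq/l, joined by *and* | Exclusion criteria |

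Assumption: creatinine is reported to one decimal, as the limits are printed. The counts below are counts of reportable values, not of patients.

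**Step 1: unit.** Since 1 dl is one tenth of a litre, mg/l ÷ 10 = mg/dl. So 2.0 mg/l = 2.0 / 10 = 0.2 mg/dl, a factor of 10 below 2.0 mg/dl. If the exclusion is taken as mg/dl, values from 0.3 to 1.9 mg/dl fail inclusion without meeting the exclusion: 19 − 3 + 1 = 17 values (at two decimals, 0.21 to 1.99: 199 − 21 + 1 = 179).

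**Step 2: boundary, with mg/dl in both lists.**

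| Creatinine (mg/dl) | Meets inclusion ≤2.0 | Meets creatinine term ≥2.0 |
|---|---|---|
| 1.9 | yes | no |
| 2.0 | yes | yes |
| 2.1 | no | yes |

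Exactly one value, 2.0, is in both lists, at one decimal or at two. As printed, with mg/l at inclusion, there is no overlap, because inclusion would stop at 0.2 mg/dl. The overlap is a consequence of correcting the unit alone.

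**Step 3: connector, with mg/dl in both lists.**

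| Creatinine (mg/dl) | Potassium (mEq/l) | Literal *and* | Two grounds |
|---|---|---|---|
| 1.0 | 6.0 | eligible | excluded |
| 2.0 | 5.0 | eligible | excluded |
| 2.0 | 6.0 | excluded | excluded |

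Take potassium above 5.5 and the 20 creatinine values from 0.1 to 2.0 that meet inclusion. A literal *and* excludes at 1 value (2.0) and passes 20 − 1 = 19. Two grounds exclude at all 20.

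**Step 4: which reading is meant.** Two grounds is the more probable one. Each condition has its own label and cut-off, the literal reading leaves the exclusion almost empty (step 3), and the endpoint list uses a similarly loose *and* in "postoperative complication rate (heart failure and respiratory failure"). Against that, the other exclusion items that join alternatives use *or*. This is the only one that joins two conditions with *and*, so the text does not settle the matter.

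**Step 5: after correction.** With inclusion <2.0 mg/dl and exclusion ≥2.0 mg/dl, 0 values are in both lists and 0 in neither.

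**The case against.** The strongest reply is that these are wording slips which no experienced site would follow literally. The neighbouring units show that mg/dl is meant. An exclusion normally overrides an inclusion, so a patient at 2.0 would be turned away on the two-grounds reading and changing ≤ to < would alter no enrolment decision. On the same reading potassium above 5.5 already excludes by itself. The value counts say nothing about patients.

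The safety link is also indirect. The limit applies before surgery, to blood that may be 90 days old, and so says little about potassium when treatment starts. The relevant control is the daily blood testing to postoperative day 7 and the monitoring under Assessment tools ("blood sodium and potassium levels and liver and renal functions will be evaluated"). Finally, the article condenses a board-approved protocol that may be worded correctly.

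Much of this stands. It keeps the point minor, it confines the hyperkalemia risk to the less probable reading, and it means that the approved text should be consulted first. It does not remove the point. The unit is wrong under any reading, nothing elsewhere in the article corrects it, and the article leaves the connector open. Monitoring limits harm after entry but does not define who may enter.

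**Conclusion.** The concern holds, as a minor one: the eligibility text is wrong as written. The unit error is a factor of 10. The overlap is a single value, 2.0 mg/dl, and arises once both limits share a unit. The connector decides whether potassium above 5.5 mEq/l excludes at every included creatinine value or only at 2.0.

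This rests on mg/dl being the intended unit and, for the value counts, on reporting to one decimal. The article gives no frequency of creatinine 2.0 or of potassium above 5.5, so the number affected among the planned 30 patients cannot be estimated and may be zero. Sample size and analysis are unaffected.

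**What to change.** First compare the article with the approved full protocol. Then, wherever the slips occur:

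- Inclusion: creatinine <2.0 mg/dl.
- Exclusion, as two separate items: creatinine ≥2.0 mg/dl; potassium >5.5 mEq/l.
- The sponsor's clinicians confirm both limits and that either condition alone excludes.

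The cost is one short wording correction. If only the article is wrong, a published correction is enough. If the approved protocol has the same wording, it needs an amendment and a check of preoperative creatinine and potassium in patients already registered. Neither case changes the sample size or the analysis.

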#### Exclusion criteria

Primary registrationPreoperatively taking tolvaptan;History of serious drug hypersensitivity or hypersensitivity to any component of tolvaptan or similar compounds;Difficulty with fluid intake or adequate hydration;Pregnant or may become pregnant;Severe ischemic heart disease or severe valvular heart disease (New York Heart Association classification ≥III);Severe hepatic cirrhosis (liver damage C);Renal dysfunction (creatinine ≥2.0) and hyperkalemia (potassium > 5.5 mEq/l);Dyspnea requiring oxygen administration due to severe respiratory impairment (Hugh–Jones classification ≥IV), interstitial pneumonia, or pulmonary fibrosis;Serious preoperative complications, such as infection or gastrointestinal bleeding;Requiring gastrointestinal anastomosis, biliary reconstruction, lymph node dissection, revascularization, or complicated resection of other organs other than the gallbladder;Psychosis or psychiatric symptoms that make study participation difficult.Secondary registrationDifficulty with fluid intake or adequate hydration;Serious postoperative complications, such as infection or gastrointestinal bleeding;Performed gastrointestinal anastomosis, biliary reconstruction, lymph node dissection, revascularization, or complicated resection of other organs other than the gallbladder.

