### Sample size calculation

In a phase III clinical trial conducted by Sakaida *et al.*
^18^ on the efficacy of tolvaptan in patients with cirrhosis with hepatic edema, weight losses were –0.44 kg (SD, 1.93) in the placebo group (*n*=80) and –1.95 kg (SD, 1.77) in the tolvaptan group (*n*=82). In a dose-ranging study of tolvaptan in patients with cirrhosis with hepatic edema conducted by Okita *et al*.^19^ weight losses were –0.36 kg (SD, 2.06) in the placebo group (n=25) and –2.3 kg (SD, 2.35) in the tolvaptan group (n=25). In other words, 1–2 kg of weight loss is expected with tolvaptan.

In our previous data, a postoperative weight gain of ~3 kg was observed patients with refractory ascites who underwent drainage of 5 ml/BW 1 kg on the first day after hepatectomy. As the same weight and ascites loss as in previous literature are expected to occur, it is assumed that the use of tolvaptan can limit postoperative weight gain to 2 kg. Assuming an SD of 2.0, an effect size of 0.5, a power of 0.9, and a significance level of 0.1, 25 cases are required; considering that the dropout rate is ~10%, 30 cases are set as the required number of cases.

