#### Observation and examination schedule

Urine output, BW, and abdominal circumference will be measured daily until discharge. Preoperative BW should be measured within 7 days prior to surgery, and BW should be measured as soon as possible after waking up. Drainage volume should be measured daily until the drain is removed. The timing of the drain removal will be at the discretion of the attending physician. Blood tests will be performed daily until 7 days postoperatively, and after 10 days at the discretion of the attending physician. Preoperative blood tests should be performed within 90 days prior to surgery. Chest radiography will be performed within 90 days before surgery, immediately after surgery, and on first, third, fifth, and seventh postoperative days. CT will be performed according to the patient’s condition. After discharge, BW and abdominal circumference measurements, blood tests, and chest radiography will be performed during outpatient visits 30 and 90 days postoperatively. The patients will also be evaluated for adverse events. Observation will be completed 90 days postoperatively.

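### The creatinine and potassium exclusions apply only before surgery; the secondary registration that admits patients to tolvaptan after hepatectomy does not repeat them

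*Protocol article*

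**What the plan says.** The protocol article has two registration steps and prints separate criteria for each.

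- **Primary registration (before surgery).** Exclusion criteria lists "Renal dysfunction (creatinine ≥2.0) and hyperkalemia (potassium > 5.5 mEq/l"). Inclusion criteria also sets a creatinine ceiling of 2.0 at this step. Observation and examination schedule allows the preoperative blood tests to be up to 90 days old at surgery.
- **Secondary registration (after surgery).** The only inclusion criterion is drainage of at least 5 ml per kg per day on postoperative day 1. There are three exclusions: difficulty with fluids, "Serious postoperative complications, such as infection or gastrointestinal bleeding", and certain additional surgical procedures.
- **Dosing.** For patients who meet the drainage criterion, "tolvaptan 7.5 mg will be added to potassium canrenoate 200 mg (or spironolactone 50 mg) starting on postoperative day 2" (Tolvaptan oral administration). Under Concomitant diuretics, "Potassium canrenoate 200 mg intravenously once daily or spironolactone 50 mg orally once daily will be the basic treatment on postoperative day 1".
- **Monitoring.** "Blood tests will be performed daily until 7 days postoperatively" (Observation and examination schedule), and "To assess patient safety, blood sodium and potassium levels and liver and renal functions will be evaluated" (Assessment tools).

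**The concern.** The sponsor set a renal and a potassium limit for entry, and a liver resection then falls between the check and the first dose. The operation can change both values, and the preoperative sample may already be old. As printed, the limits screen the preoperative patient and not the patient about to be dosed.

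The article itself links diuretics to these values. Its Introduction notes renal deterioration and mineral abnormalities with high-dose spironolactone, and its Discussion mentions diuretic-induced acute kidney injury. Statistical analysis makes safety part of the primary objective.

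Two things are at stake. A patient outside the protocol's own limits may be treated without breaching any numeric criterion. And whether such a patient is treated depends on one clinician's view of what is serious, so similar patients may be handled differently in a single-arm study of 30.

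**Working it through.** The plan gives no figure on this point to reproduce. The check is a comparison of the two lists, followed by a rough sizing.

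**Step 1. Which exclusions cross from primary to secondary registration?**

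| Primary exclusion | At secondary registration |
|---|---|
| Difficulty with fluids | Repeated unchanged |
| Serious preoperative complications | Reworded as postoperative |
| Additional procedures required | Reworded as performed |
| Creatinine ≥2.0, potassium >5.5 mEq/l | Absent |

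**Step 2. Could the serious-complications item stand in for the missing one?** At primary registration the renal and potassium item stands beside a parallel serious-complications item, so the protocol treats them as separate there. The postoperative version gives infection and gastrointestinal bleeding as examples and has no laboratory threshold. It could catch overt renal failure or severe hyperkalemia. It does not fix what happens to a patient moderately over either limit.

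**Step 3. Are the values available in time?** Yes. Blood is tested daily to day 7 and tolvaptan starts on day 2, so a day 1 result can be used. What is missing is a value tied to starting treatment.

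**Step 4. Rough size.** Let p be the share of drain-positive patients over either limit on day 1. The documents do not give p, so 1%, 5% and 10% are assumed. The 30 patients come from Sample size calculation.

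- Expected number among 30 treated = 30 × p
- Chance of at least one = 1 − (1 − p)^30
- Drain-positive patients needed to register 30 under the fix = 30 / (1 − p)
- Shift in the treated mean = p × d, with d = 2 kg assumed (one planning SD) as the difference in mean weight change between those patients and the rest

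| p (assumed) | Expected in 30 | At least one | Needed to register 30 | Shift in mean |
|---|---|---|---|---|
| 1% | 0.3 | 1 − 0.99^30 = 26% | 30 / 0.99 = 30.3 | 0.02 kg |
| 5% | 1.5 | 1 − 0.95^30 = 79% | 30 / 0.95 = 31.6 | 0.10 kg |
| 10% | 3.0 | 1 − 0.90^30 = 96% | 30 / 0.90 = 33.3 | 0.20 kg |

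The planned difference is 3 − 2 = 1 kg, so even the largest assumed shift is a fifth of it.

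**The case against.** **The omission may be deliberate.** The article hypothesises that tolvaptan protects renal function, so patients whose creatinine rises after surgery may be of interest. That is a reason to choose a different postoperative limit and state it. It does not explain having a preoperative limit and none at dosing.

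**Other laboratory limits are not repeated either.** White cells, hemoglobin, platelets and bilirubin also appear only at primary registration, which suggests a consistent pattern of laboratory screening before surgery and clinical criteria after it. This is a fair description. Creatinine and potassium still stand apart, because they form an explicit exclusion and bear directly on the diuretics being given.

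**Safeguards exist.** The serious-complications item is open-ended, blood is drawn daily, potassium and renal function are evaluated for safety, and the study has one center. All of this stands and lowers the risk. None of it ties a value to the first dose, and one center can still have several attending physicians.

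**An article condenses the protocol.** True in general, but here both registration lists are printed item by item, and three exclusions were carried into the second.

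**Excluding a patient from tolvaptan does not stop the potassium-retaining drug.** This is correct, and it limits what the fix does for potassium. A reader might go on to ask for a potassium rule for the background diuretic, including in patients who fail secondary registration, since the article says only that "Similar to tolvaptan, potassium canrenoate can be reduced or discontinued as required as symptoms improve". The document does not support that step. Concomitant diuretics does not address patients who are not registered, and hold rules for a concomitant drug are detail that an article commonly leaves to the full protocol.

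**Conclusion.** The point holds for the criteria as printed. The limits are set before surgery and are not re-applied at the step that releases tolvaptan, and the existing safeguards cover the gap only in part. The sponsor should close it, on grounds of safety and consistent eligibility.

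The frequency is unknown. The 26% to 96% chance of at least one affected patient rests wholly on the assumed shares of 1% to 10%.

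A reader might infer that the primary endpoint is biased, or that the historical reference ("a postoperative weight gain of ~3 kg was observed patients with refractory ascites") must be recomputed with the same exclusions. The documents support neither. Under the assumptions above the mean shifts by 0.02 to 0.20 kg against a planned 1 kg, and recomputing the reference would need day 1 laboratory data from a series that is not shown. Nor is it the case that postoperative renal function and potassium go unmonitored: they are evaluated, but not used as a criterion for starting.

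**What to change.** Add one line to the secondary-registration exclusions: *creatinine ≥2.0 mg/dl or potassium >5.5 mEq/l on the postoperative day 1 blood test*. The unit is assumed, because the exclusion prints none. The word *or* makes either value sufficient. If the sponsor considers higher values acceptable after hepatectomy, a different numeric limit with a short justification would serve equally well.

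**Cost.** No extra sampling, because blood is already drawn daily to day 7. Some drain-positive patients may fail secondary registration: at the assumed shares, 0.3 to 3.3 more would be needed to register 30. The treated group may also differ slightly from the ~3 kg reference, which Sample size calculation describes by day 1 drainage without any laboratory limit.
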